### Participant

2.1

We are preparing a double-blind, sham-controlled research project with two randomized subgroups aimed at investigating the clinical effectiveness of a augmented iTBS protocol for the treatment of schizophrenia. Based on a recent meta-analysis of frontal cortex rTMS for improvement of schizophrenia (21), we assumed an effect size of 0.64. Using this assumption and the baseline values as covariates, we concluded that with a power equal to or greater than 80% (β= 0.20), there was a significant difference between the two groups in terms of improvement in cognitive function (α = 0.05), a sample size of 62 calculated using G*Power, and we expected a dropout rate of 10%. Therefore, we plan to include 70 patients who met the DSM-V diagnostic criteria for schizophrenia. We will assign patients to the active stimulation and sham stimulation groups in a 1:1 ratio, and patients participating in the study will be given sequentially numbered patient codes to which the corresponding treatment modality (active or sham stimulation) will be assigned (**Figure 1**). The subjects for this study will be recruited from the inpatients of Zigong Mental Health Centre, who need to meet all the inclusion criteria and not meet any exclusion criteria.

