#### Primary outcome

2.7.1

Our primary outcome will be the mean change scores of cognitive function assessed using RBANS from baseline to the end of the treatment period. The RBANS, developed by Randolph in 1998, assesses five cognitive domains through 12 subtests, including Attention (Digit Breadth and Encoding Tests), Verbal (Picture Naming and Semantic Fluency Tests), Visual Breadth (Picture Copying and Line Orientation Tests), Immediate Memory (Vocabulary Acquisition and Story Repetition Tests), and Delayed Memory (Vocabulary Recall, Vocabulary Re-recognition, Story Recall, and Picture Recall Tests). We expect that patients receiving active stimulation will show significant improvements in performance on these tests, scoring higher on the total score of the RBANS than the sham stimulation group.

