We will use fNIRS technology to record the changes in hemoglobin concentration in the prefrontal cortex during the semantic Verbal Fluency Task (VFT). The VFT is a neurocognitive task commonly used in fNIRS studies and can be divided into phonological and semantic VFTs. The semantic VFT in this experiment will be divided into four phases, and each phase will consist of a 30s resting period and a 30s task period, with a 70s resting period at the end, for a total of 310s (**Figure 4**). During the resting period, the participants will be asked to repeatedly count ‘1, 2, 3, 4, 5’, and during the task period, they will be asked to say as many words as possible belonging to the categories of ‘four-legged animals…’, ‘fruits…’, ‘household appliances’, and ‘vegetables’, respectively, and the researcher recorded the number of words that were correct without repetition. The researcher will record the number of correct words without repetitions. Before starting the task, the participants will be given a practice session to ensure that they understood the task. A meta-analysis has shown that patients with multiple psychiatric disorders experience hypoactivation (e.g., decreased ΔHbO) in relevant brain regions during the VFT task, which may be associated with impaired cognitive function (26). Therefore, we plan to compare fNIRS responses between the two groups, and we expect greater activation in relevant brain regions in the active stimulation group.

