### Statistical analysis of data

2.8

The normality of the measures will be assessed using the Shapiro-Wilk test. The Levene test will be used to assess the conformity of the variance of the measures. Two independent samples t-test will be used for measures that met normality. The Mann-Whitney U test will be used for measures that did not meet normality. Categorical variables will be analyzed using the chi-square test. Pearson’s correlation analysis will be used to explore the relationship between cognitive function improvement and changes in neural activity. P-value <0.05 will indicate a statistically significant difference.

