## Discussion

3

This study is a double-blind, sham-controlled, parallel-group trial designed to investigate the effects of augmented iTBS on the L-DLPFC and its associated cerebral cortical oxyhemoglobin levels, in patients with schizophrenia using fNIRS techniques. Given the causal relationship between cognitive deficits and impaired daily functioning in patients with schizophrenia and the potential of rTMS as a cognitive enhancement treatment, an in-depth understanding of the mechanisms of action of rTMS in schizophrenia is essential for optimizing interventions (6). The exact mechanism by which rTMS positively affects cognition is not yet known. Neuropsychological evidence suggests that the frontal lobes play a key role in social cognition, and that rTMS targeting the L-DLPFC in patients with schizophrenia may enhance cognitive processing (14). Clarifying the relationship between prefrontal modulation and cognitive improvement will provide a framework for interventions, as prefrontal cognitive deficits are the root of much of the disability in schizophrenia. The results of this study could help optimize rTMS protocols for the treatment of schizophrenia and provide insight into the neurocognitive mechanisms underlying the interventions.

fNIRS is a noninvasive neuroimaging technique that indirectly reflects neural activity by measuring changes in oxyHb and deoxyHb in the cerebral cortex. Increased neuronal activity in a brain region leads to elevated local blood flow, typically characterized by higher oxyHb and lower deoxyHb levels (29), which fNIRS can detect to infer brain activation. fNIRS-derived measures of cerebral oxygenation (e.g., changes in oxyHb and deoxyHb) hold promise as potential biomarkers for schizophrenia. Several studies have found significant differences in activation patterns or hemodynamic parameters in specific brain regions in patients with schizophrenia (30, 31), and these differences may help in the early diagnosis of schizophrenia or in distinguishing between different subtypes of patients. Furthermore, this technique has been widely applied to monitor cognitive function during rehabilitation in patients with stroke and brain injury (18).

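### Section 2.8 names a Pearson correlation between cognitive and neural change without saying how treatment arm is handled; if both arms are pooled, two separate treatment effects can look like a brain-cognition link

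*Protocol article*

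**What the plan says.** The protocol article gives the brain-cognition analysis one sentence in section 2.8 (Statistical analysis of data): Pearson's "correlation analysis will be used to explore the relationship between cognitive function improvement and changes in neural activity". A general significance threshold of p<0.05 follows, and the correlation is not exempted from it. The section names no arm term, no stratification and no covariate for this analysis. Nor does it say whether the coefficient is computed over all participants or within each arm.

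The outcome sections predict an effect of stimulation on both variables. For RBANS (2.7.1), active patients are expected to improve, "scoring higher on the total score of the RBANS than the sham stimulation group". For fNIRS (2.7.2), "we expect greater activation in relevant brain regions in the active stimulation group". The Discussion then attaches a mechanistic purpose to the link: "Clarifying the relationship between prefrontal modulation and cognitive improvement will provide a framework for interventions".

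**The concern.** Under the trial's own hypotheses, arm is a common cause of both variables in the correlation. When two groups differ in mean on both variables, pooling them produces a correlation from the group difference alone. A significant pooled coefficient therefore cannot be told apart from two unrelated treatment effects, and this happens precisely when the trial succeeds on both outcomes.

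Section 2.8 gives no other analysis that links fNIRS change to cognitive change. What is at stake is how that link may be interpreted. The comparisons between arms are not at stake.

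**Working it through.** **Inputs from the article**
- Effect on cognition: "we assumed an effect size of 0.64" (section 2.1), read here as a standardised mean difference.
- Sample size: "with a power equal to or greater than 80% (β= 0.20" and "α = 0.05), a sample size of 62 calculated using G*Power" (section 2.1). With 1:1 allocation, 62 is 31 per arm; 70 are enrolled, or 35 per arm.
- Threshold: p<0.05 (section 2.8), taken as two-sided for the correlation.

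**Assumptions, not in the article**
- No association between the two changes within either arm.
- Size of the fNIRS effect. None is given, so a range is used.
- Normal changes with SD 1 within arm.

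**The article's own figure.** The article gives no figure for the correlation. Its 62 is used here only to set N. A one-sided two-sample t-test with d = 0.64 and 31 per arm has power 0.801, which reproduces 62. A two-sided test needs 80, or about 62 with baseline as covariate and a baseline correlation between 0.45 and 0.50. Sidedness is a separate matter. For dropout, 62/0.9 = 68.9, so 69, or 70 when made even.

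**Step 1: induced correlation.** With equal arms and zero within-arm correlation, the pooled covariance is d1·d2/4 and each pooled variance is 1 + d²/4. Hence

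r = (d1·d2/4) / √[(1 + d1²/4)(1 + d2²/4)]

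- 0.64 and 0.64: 0.1024/1.1024 = 0.093
- 0.64 and 1.0: 0.16/√(1.1024 × 1.25) = 0.16/1.174 = 0.136
- 1.0 and 1.0: 0.25/1.25 = 0.20
- 0.64 and 0: 0

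**Step 2: chance of p<0.05.** Simulation with 40,000 runs per row, two-sided 0.05. The adjusted column is the partial correlation given arm, at N = 62.

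| Effects (SD) | Pooled r | Pooled, N = 62 | Pooled, N = 70 | Adjusted for arm, N = 62 |
|---|---|---|---|---|
| 0.64 / 0 | 0 | 4.9% | 5.2% | 5.0% |
| 0.64 / 0.64 | 0.093 | 11.2% | 11.9% | 5.0% |
| 0.64 / 1.0 | 0.136 | 19.0% | 20.4% | 5.1% |
| 1.0 / 1.0 | 0.20 | 35.2% | 39.0% | 5.1% |

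**Step 3: hand check of the 0.64/0.64 row.** Fisher's z for r = 0.093 is 0.0932. The standard error is 1/√(62 − 3) = 0.130, so the shift is 0.0932/0.130 = 0.72. Then P(Z > 1.96 − 0.72) + P(Z < −1.96 − 0.72) is about 0.107 + 0.004 = 0.11, which agrees with the simulation.

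**Step 4: the opposite distortion.** Pooling can also hide an association. With within-arm r = −0.20 and effects of 1.0 on both outcomes, pooled r = (−0.20 + 0.25)/1.25 = +0.04.

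**The case against.** The strongest reply is that section 2.8 never says the arms are pooled. A Pearson correlation computed within each arm fits the sentence too and has no such problem, and a condensed article may leave the choice to a fuller document. This stands in part. A reader might infer that the plan ignores arm, but the article does not say that; it states no handling of arm. The point still holds because the method is named, and the default use of that method is the one that misleads.

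Several other limits stand:
- The analysis is there to explore, and it is neither the primary nor a listed secondary outcome. A reader might infer that the trial's main result is compromised. It is not: the group comparisons of RBANS, PANSS negative score and fNIRS do not use this correlation.
- The higher rejection rates need effects above the only one the article states. The 35% should not be read as the expected rate.
- When both outcomes move, the pooled correlation really is non-zero, so rejecting zero is not strictly a type I error for the pooled coefficient. It is an error only if the result is read as a link within arms, so the fault lies in the interpretation.
- The Discussion sentence is an aspiration and does not cite this correlation. It shows how the result is likely to be used, not that the argument depends on it.
- Section 2.8 provides a rank test for group comparisons ("The Mann-Whitney U test will be used for measures that did not meet normality") but names no rank version here. That could be read as a contradiction. It is not one, because the switch is written for comparing groups, so this is an optional refinement.

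**Conclusion.** The point holds as a minor one. Section 2.8 should say how arm is handled, because a coefficient pooled over both arms could not support a mechanistic reading if stimulation moves both outcomes.

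At the article's own 0.64 SD, applied to both outcomes, the induced correlation is small (0.09), but the chance of a nominally significant result roughly doubles, from 5% to about 11%. It reaches about 19% to 35% only if one or both effects are as large as 1.0 SD, and there is no inflation if only one outcome moves. These figures rest on pooling, zero within-arm correlation, 31 per arm and an fNIRS effect that the article does not give.

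**What to change.** Amend the sentence in 2.8 to say that the association between RBANS change and oxyHb change will be estimated adjusted for arm. This can be a partial correlation given arm, or a linear model of RBANS change on oxyHb change with arm as a term. Show the two within-arm estimates beside it, and label any coefficient pooled over both arms as descriptive.

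Baseline RBANS and baseline oxyHb may be added as covariates, but as a separate model: conditioning on them answers a different question from the partial correlation given arm. Optionally, name a rank-based version for use if normality fails.

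The cost is one sentence, no new data and about one degree of freedom for arm (59 instead of 60 at N = 62), plus about one more for each added covariate. The article reports that recruitment is still open, so the sentence can be settled before unblinding.

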### Analysis sets

2.9

We will use the following analysis sets:

1. The intention-to-treat (ITT) analysis set will include all participants who were randomly assigned to a treatment group, irrespective of treatment adherence or study completion. This approach aims to assess the treatment effect under real-world conditions by providing a conservative estimate of efficacy that accounts for non-adherence and dropout, thereby reducing bias and reflecting the treatment’s potential effectiveness in clinical practice.2. Safety analysis set: This will consist of a subset of participants in the randomized analysis set who will have received at least one pulse stimulation treatment with at least one safety evaluation.3. Per-protocol analysis set: This will consist of a subset of subjects in the full analysis set who will be at least 80% compliant (having received 80% of the planned stimuli) and will not have any program bias, which is considered to have a substantial impact on the primary efficacy outcome.

### Withdrawal of patient from study

2.10

Patients may withdraw from the study at any time for any reason without affecting their future medical care by the investigator or study site. Every effort will be made to keep the patient in the study by documenting the reasons why the patient did not complete the treatment and/or did not complete the study. Patients may withdraw from the study for any of the following reasons:

Noncompliance with the protocol or serious breach of the protocol.Severe or intolerable adverse event (AE).Failure to follow up.Withdrawal of consent by the patient.Adjustment of the medication regimen or receipt of Modified Electroconvulsive Therapy (MECT) during the study.

When a patient withdraws from active participation in the study, the investigator will document the reason for discontinuation on the relevant page of the Case Report Form. If possible, all patients who discontinue treatment or withdraw from the study early will be assessed at the time of the early withdrawal visit. The investigator should make diligent efforts and explore all possible options to contact patients who fail to attend the visits. It is crucial to obtain follow-up data from any patient who withdraws from the study due to an AE. If a patient must withdraw from the study because of a SAE, the patient will be followed up until the condition is stable or the event is no longer considered clinically significant. In each case, efforts must be made to conduct the safety and follow-up procedures as specified in the protocol.

## Discussion

3

This study is a double-blind, sham-controlled, parallel-group trial designed to investigate the effects of augmented iTBS on the L-DLPFC and its associated cerebral cortical oxyhemoglobin levels, in patients with schizophrenia using fNIRS techniques. Given the causal relationship between cognitive deficits and impaired daily functioning in patients with schizophrenia and the potential of rTMS as a cognitive enhancement treatment, an in-depth understanding of the mechanisms of action of rTMS in schizophrenia is essential for optimizing interventions (6). The exact mechanism by which rTMS positively affects cognition is not yet known. Neuropsychological evidence suggests that the frontal lobes play a key role in social cognition, and that rTMS targeting the L-DLPFC in patients with schizophrenia may enhance cognitive processing (14). Clarifying the relationship between prefrontal modulation and cognitive improvement will provide a framework for interventions, as prefrontal cognitive deficits are the root of much of the disability in schizophrenia. The results of this study could help optimize rTMS protocols for the treatment of schizophrenia and provide insight into the neurocognitive mechanisms underlying the interventions.

fNIRS is a noninvasive neuroimaging technique that indirectly reflects neural activity by measuring changes in oxyHb and deoxyHb in the cerebral cortex. Increased neuronal activity in a brain region leads to elevated local blood flow, typically characterized by higher oxyHb and lower deoxyHb levels (29), which fNIRS can detect to infer brain activation. fNIRS-derived measures of cerebral oxygenation (e.g., changes in oxyHb and deoxyHb) hold promise as potential biomarkers for schizophrenia. Several studies have found significant differences in activation patterns or hemodynamic parameters in specific brain regions in patients with schizophrenia (30, 31), and these differences may help in the early diagnosis of schizophrenia or in distinguishing between different subtypes of patients. Furthermore, this technique has been widely applied to monitor cognitive function during rehabilitation in patients with stroke and brain injury (18).

In addition, this study will provide preliminary safety and efficacy data on augmented iTBS treatment protocol to support future larger clinical trials. Positive results may drive more extensive testing of this promising tool to alleviate the severe symptoms affecting most people with schizophrenia. In conclusion, this study will integrate multiple approaches to optimize noninvasive brain stimulation for cognitive enhancement in schizophrenia, highlighting its critical importance as a therapeutic strategy for this disorder.

## Trail status

4

The protocol version number is V1.0, and the date is July 23, 2025. The Ethics Committee of Zigong Mental Health Center approved the study protocol on August 2,2025(approval number 20250802). The trial was registered on August 21,2025(ChiCTR2500107943). The trial started on September 1, 2025. The trial is currently recruiting participants. We predict that the recruitment will be completed by January 31, 2026.
